# The effect of implementing an aseptic practice bundle for anaesthetists to reduce postoperative infections, the Anaesthetists Be Cleaner (ABC) study: protocol for a stepped wedge, cluster randomised, multi-site trial

**DOI:** 10.1186/s13063-019-3402-8

**Published:** 2019-06-10

**Keywords:** Postoperative infection, Anaesthesia, Surgery, Patient safety, Prevention, Stepped wedge, Cluster randomised

## Abstract

**Background:**

Postoperative infection is a serious problem in New Zealand and internationally with considerable human and financial costs. Also, in New Zealand, certain factors that contribute to postoperative infection are more common in Māori and Pacific populations. To date, most efforts to reduce postoperative infection have focussed on surgical aspects of care and on antibiotic prophylaxis, but recent research shows that anaesthesia providers may also have an impact on infection transmission. These providers sometimes exhibit imperfect hand hygiene and frequently transfer the blood or saliva of their patients to their work environment. In addition, intravenous medications may become contaminated whilst being drawn up and administered to patients. Working with relevant practitioners and other experts, we have developed an evidence-informed bundle to improve key aseptic practices by anaesthetists with the aim of reducing postoperative infection. The key elements of the bundle are the filtering of compatible drugs, context-relevant hand hygiene practices and enhanced maintenance of clean work surfaces.

**Methods:**

We will seek support for implementation of the bundle from senior anaesthesia and hospital leadership and departmental “champions”. Anaesthetic teams and recovery room staff will be educated about the bundle and its potential benefits through presentations, written material and illustrative videos. We will implement the bundle in operating rooms where hip or knee arthroplasty or cardiac surgery procedures are undertaken in a five-site, stepped wedge, cluster randomised, quality improvement design. We will compare outcomes between approximately 5000 cases before and 5000 cases after implementation of our bundle. Outcome data will be collected from existing national and hospital databases. Our primary outcome will be days alive and out of hospital to 90 days, which is expected to reflect all serious postoperative infections. Our secondary outcome will be the rate of surgical site infection. Aseptic practice will be observed in sampled cases in each cluster before and after implementation of the bundle.

**Discussion:**

If effective, our bundle may offer a practical clinical intervention to reduce postoperative infection and its associated substantial human and financial costs.

**Trial registration:**

Australian New Zealand Clinical Trials Registry, ACTRN12618000407291. Registered on 21 March 2018.

**Electronic supplementary material:**

The online version of this article (10.1186/s13063-019-3402-8) contains supplementary material, which is available to authorized users.

## Background

Postoperative infection, which includes surgical site infection, pneumonia and sepsis, is a serious problem internationally with considerable human and financial costs [1, 2]. In New Zealand (NZ) alone the cost of postoperative infections exceeds NZ$136 million per year [1]. Surgical site infection occurs in up to 5% of “clean” operations [3]. Patients may face weeks with discharging wounds, time off work and re-admission to hospital [4]. In some cases, implanted artificial joints or heart valves may need to be removed and replaced. Haematogenous seeding of infection may lead to pneumonia. In the worst cases, sepsis may develop, with widespread inflammation, damage to organs and sometimes life-threatening “septic shock”.

In May 2017, the 70th World Health Assembly adopted a resolution on sepsis, urging member states “to reinforce existing strategies or develop new ones leading to strengthened infection prevention and control programmes, including… ...infection prevention practices in surgery” [5]. This followed a 2015 statement from the Lancet Infectious Diseases Commission which emphasised the global burden of sepsis and stressed global concerns over increasing pathogen resistance to antimicrobial therapies [6]. Worryingly, postoperative sepsis has increased in NZ from 7 per 1000 at-risk admissions between 2005 and 2009 to 11 per 1000 in 2013 [7]. The prevention of sepsis starts with the prevention of infections in general, notably after surgery. Thus, in NZ, reducing surgical site infection is a priority for the Health Quality & Safety Commission, the Accident Compensation Corporation, the Ministry of Health and the country’s district health boards, with national programmes implemented to this end. In 2016–2017, 28% of the Accident Compensation Corporation costs (NZ$15 million out of NZ$55 million) attributed to personal injury suffered during medical treatment were directed towards infections following surgery [8].

There is reason to believe that the burden of infective postoperative complications may not be distributed homogenously in NZ. For example, ethnic disparities in healthcare outcomes are substantial: health outcomes are, in general, worse in Māori and Pacific peoples than in their non-Māori/non-Pacific counterparts [9, 10]. Some factors identified as contributing to infection after surgery, including comorbidities such as obesity, diabetes [11] and skin infections, are more prevalent in Māori and Pacific populations [4, 12]. In addition, there could be differences in relevant aspects of their care both within hospital [13, 14] and outside hospital (e.g. access to care for wound reviews after going home from hospital). It therefore seems likely that Māori and Pacific peoples are at higher risk of postoperative infection.

Efforts to reduce postoperative infection have traditionally focussed on aspects of surgical technique and care, on hand hygiene, and on antibiotic prophylaxis. However, researchers in the United States [15–21] have recently demonstrated that anaesthesia providers also have a direct impact on bacterial transmission and infection rates in surgical patients. It is relevant that the work of anaesthetists may be very demanding. For example, anaesthetists administer a surprisingly high number of intravenously delivered medications (on average ten injections per patient [22] and frequently more), often under considerable time pressure. Similarly, techniques involved in securing patients’ airways to ensure adequate oxygenation after the administration of neuro-muscular blocking medications may be time-critical and technically difficult. In this setting, hand hygiene and the management of contaminated airway equipment may sometimes seem secondary to other more pressing requirements to keep patients alive. Anaesthetists’ hands frequently contact patients’ saliva whilst securing the airway, and blood during the insertion of lines into veins and arteries. Hand hygiene practices may be performed less than once per hour [16]. Anecdotal observation suggests that gloves are often seen as a substitute for hand hygiene and that, under pressure of workflow, anaesthetists often move from tasks that contaminate their gloves to adjusting their anaesthetic machines, handling syringes or undertaking various other activities. Similarly, contaminated laryngoscopes and other instruments may be inadvertently returned to clean surfaces rather than designated contaminated trays. One way or another, anaesthetists can rapidly and widely contaminate their work environment [17].

Cole et al. found that 12–16% of multi-use injection ports through which medications are administered contain bacteria within 6 h [23]. Crucially, Loftus et al. have demonstrated an association between contamination of these ports and postoperative mortality [20] and transmission of pathogenic bacteria from one patient on an operating list to another, including transmission via the hands of providers and environmental surfaces [24]. Recent data from our own group [25, 26] suggest that the methods by which anaesthetists typically draw up and adminster intravenous (IV) medications during surgery may be underestimated as a contributor to postoperative infection. In highly realistic simulated surgical cases using real medications and standard practices, our group cultured gram positive, gram negative and other micro-organisms associated with postoperative infections from 5 of 38 bags (13%) of collected injectate from IV medications [25]. Then, in a clinical setting at Auckland City Hospital, we asked anaesthetists to inject their IV bolus medications via a 0.2-μm filter unit inserted into the IV line of 300 patients undergoing surgery [26]. We isolated similar micro-organisms from 6% of these filters and from 2.4% of syringes retained for possible reuse during the anaesthetics. Thus, the injection of micro-organisms into patients may arise from deficiencies in aseptic techniques in the handling of IV medications as well as from contamination of IV injection ports. Loftus et al. have investigated the use of novel devices for hand sanitisation, device disinfection, IV catheter management and stopcock design, and demonstrated reduced bacterial contamination leading to a decrease in postoperative infection [16, 19, 21]. However, these approaches may not address failures in aseptic technique during the drawing up and injecting of IV medications. All sources of infection associated with these processes could be simultaneously and substantially addressed by injecting all IV boluses of medications through a commercially available 0.2-μm filter unit of the sort often used with epidural injections. Even if the injection port on one of these units becomes contaminated, it will be proximal to a filter that is fine enough to capture most micro-organisms [27]. We have shown that it is practicable for anaesthetists to inject most IV medications through these filters, with a rated difficulty of 3 out of 10 (10 being the most difficult) [26].

Unfortunately, it is not possible to manage the commonly used anaesthetic induction agent propofol in this way. Propofol is typically provided in lipid emulsion, composed of droplets with a mean (range) size of 0.19 (0.15–0.3) μm [28], and the manufacturers (Fresenius Kabi, AstraZeneca, and AFT Pharmaceuticals) recommend that the emulsion should not be injected through microbiological filters (manufacturers’ product information sheets). This is particularly problematic, because lipid emulsions provide a rich source of nutrients for bacterial growth. An association between propofol and postoperative infections began to be reported in the early 1990s [29–33]. In response, the then manufacturer provided an extensive educational programme for anaesthesia personnel and changed the product information to include explicit handling instructions. These instructions included using alcohol to decontaminate the neck of ampoules or rubber bungs of vials, drawing up the emulsion “aseptically”, maintaining single patient use and replacing infusion systems after 6 h [32]. Ethylenediaminetetraacetic acid (EDTA) was added to the formulation in 1996 [34]. EDTA does not prevent micro-organisms from contaminating the formulation, but it does retard their growth [35]. The product currently available in NZ does not contain any preservative and is presented in both vials and ampoules.

It seems, therefore, that a multi-faceted approach is called for to address the potential contribution of anaesthesia providers to postoperative infection. A strong precedent for the potential of a bundle of measures to reduce infection is to be found in the “Keystone Project”. This project involved strict adherence to a few simple, evidence-based practices in the insertion and subsequent management of central venous lines which substantially and sustainably reduced the median rate of catheter-related bloodstream infections per 1000 catheter days (from 2.7 pre-intervention to zero at 3 months) [36]. Widespread implementation of this bundle has been associated with reductions in mortality [37] and healthcare costs [38]. Impressive results were again obtained in a more recent study focussed on reducing catheter-associated bloodstream infections in patients with a bundle of care delivered by their intraoperative anaesthetic providers [39].

A key aspect of the “Keystone Project” was its use of the principles of implementation science [36]. Similar principles have been articulated in the recent World Health Organization publication “Guidelines on Core Components of Infection Prevention and Control Programmes” [40]. Drawing from these sources, guiding principles have been developed for this study (Table 1).

**Table 1 Tab1:** The principles of implementation science guiding this study (adopted from Pronovost et al. [36])

1	The relevant practitioners should agree that the problem matters, and therefore that the response is warranted.
2	The evidence supporting or informing the requested practices should be convincing.
3	The tasks required should make sense, be possible to perform and preferably be easy to do.
4	Buy-in and support should be obtained at all levels, notably from practitioners and from senior clinical and managerial leadership: to this end as much engagement as possible should occur with all relevant participants at every stage of the implementation process.
5	Once the intervention has been agreed to, compliance should not be negotiable.

In line with principles 2, 3 and 4, we have worked collaboratively with anaesthetists, anaesthetic technicians, microbiologists and others from each of our study hospitals to develop an evidence-informed, multi-faceted practicable infection prevention bundle (see the following subsection) which combines a selection of key aseptic practices with the routine use of 0.2-μm filters for all IV bolus medications administered during anaesthesia, except propofol. We now aim to implement our bundle progressively in these institutions as a quality improvement project and to evaluate the impact of this implementation on the rate of postoperative infection.

### The development of the infection prevention bundle

Candidate elements for our infection prevention bundle were identified through a preliminary process of literature review and consultation with a group of relevant practitioners and other experts. A focus group meeting was then held with anaesthetists and anaesthetic technicians from each participating department. Rather than priming the participants with a suggested bundle, an open-ended invitation was given to make any suggestions on how to improve aseptic practices relevant to anaesthesia and to discuss any aspects relevant to any putative bundle. The importance of practicability and ease of implementation was emphasised by the facilitator, and no suggestions were disallowed. Notes were taken, and the preliminary bundle was modified by the investigators on the basis of reflection on this discussion. A second focus group was then held at which participants were presented with a draft of a proposed bundle. They were asked to comment on and discuss each aspect of this bundle. Notes were taken again. A penultimate draft of the bundle was then prepared, reflecting the published evidence, the discussions at both focus groups, the practicality and acceptability of each element of the bundle and the likely impact of these elements on postoperative infection.

### Primary hypothesis

We hypothesise that the implementation of a bundle that combines a selection of key aseptic practices with the routine use of 0.2-μm filters for all IV bolus medications administered during anaesthesia except propofol will reduce clinically relevant postoperative infections in a targeted group of high-risk patients. “Clinically relevant” in this context implies infections severe enough to require additional hospitalisation or death.

## Methods

### Ethics approval and informed consent

Approval has been obtained from the NZ Northern B Health and Disability Ethics Committee on the basis that this study will be an evidence-informed, quality improvement initiative and will not require informed consent from individual patients, because patient data will be used in an anonymous form, and the intervention is low risk. Instead we will obtain consent from participating anaesthetists, anaesthetic technicians and perfusionists, as recommended by Weijer et al. (2012) [41]. We will also seek site approval from each participating hospital, support from senior hospital leadership and agreement from participating departments to take part in the study.

### Design

Our study does not lend itself to the randomisation of individual cases. Instead, we will randomise clusters. To maintain separation of anaesthetists following usual practice from those who have adopted the aseptic practices in our bundle, we will cluster by departments. This implies a small number of large clusters. Quite substantial differences in practices and case mix may exist between departments, so intracluster correlation is likely to be quite high. Thus, we will use a real-world, multi-site, stepped wedge, cluster randomised quality improvement design (with five clusters) to compare outcomes when participants employ usual anaesthetic practices to outcomes when our bundle is adopted [42]. The stepped wedge design is ideal for progressive implementation of quality improvement initiatives such as the one in this study, and will also be more statistically efficient than alternative cluster designs because of our anticipated high intracluster correlation.

We will exclude data from our analysis for 1 week following transition from baseline to active phases of the study at each site to allow for the influence of progressive uptake of the bundle and the required changes in participating anaesthetists’ practice.

### Structure of the stepped wedge

All five sites will begin the study simultaneously on the first step, which will consist of normal care. Each step (in which one department adopts the bundle) will occur 6 months (180 days) after the previous one. Thus, at the end of the first 6 months the first site will adopt the bundle, whilst the other four sites continue with normal practice for another 6 months. The remainder of the sites will sequentially adopt the bundle in order; one every 6 months until 6 months after the start of the final (sixth) step. During the last 6 months all sites will be using the bundle.

The 6-month duration of the steps has been chosen because it allows enrolment of an adequate number of cases (see Statistics and sample size section), it ensures an adequate period within each new step for the bundle to become properly embedded and it allows sufficient intervals between steps for the rollout plan for each new step to be assiduously followed in an unhurried manner.

### Setting and participants

The study will be conducted in five departments (our clusters) in four large metropolitan hospitals in Auckland, NZ: Auckland City Hospital, Starship Children’s Hospital, Middlemore Hospital and North Shore Hospital (see Additional file 1: Table S1). The participants will be the clinical teams providing anaesthesia, perfusion and immediate postoperative care in the recovery unit for patients undergoing hip or knee arthroplasty or cardiac surgery in these hospitals during the duration of the study. These surgical subgroups have been chosen because these patients are subject to moderately high rates of postoperative infection, and the consequences of infection when it occurs are devastating — for example, implanted prostheses may need removal after arthroplasty, and sternal wounds may dehisce after cardiac surgery. Furthermore, well-developed systems for reporting surgical site infection to national databases are in place for these patients. We will be seeking approval for the study from senior hospital leadership and agreement in principle from participating departments to participate in the study, so it seems unlikely that an individual department will not adhere to the implementation of the bundle.

The projected case numbers per year have been taken from Surgical Site Infection Improvement Programme, national orthopaedic and cardiac surgical site infection reports (available from www.hqsc.govt.nz).

### Inclusion criteria

All hip or knee arthroplasty or cardiothoracic surgery (as defined by the Surgical Safety Infection Improvement Programme [43]) procedures will be carried out in the five clusters under general anaesthesia with or without regional anaesthesia, or under regional anaesthesia with sedation. Participant anaesthetists, anaesthetic technicians and perfusionists who consent to be part of the study will be included.

### Exclusion criteria

Patients receiving organs for heart and lung transplants will be excluded from the study because of their complexity and the use of immunosuppression in these cases. Likewise, patients donating organs for these purposes (i.e. patients who are classified as American Society of Anesthesiologists [ASA] 6) will be excluded. Participant anaesthetists, anaesthetic technicians and perfusionists who decline to be part of the study will be excluded.

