### Withdrawal criteria

Participating anaesthetists will be expected to act in the best interests of their patients, and so will be free to withdraw individual cases or to omit any aspect of the bundle (for example, the use of the filter) if they believe this is warranted. Participants will be free to withdraw from the study. They will be asked to report any such decisions to the investigators.

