**Fig. 2 Fig2:**
[figure not shown]
SPIRIT figure showing schedule of enrolment, interventions and assessments. Baseline data collection will be from 20 May 2018

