### Trial status

We are at Protocol version 1.3 (04 Sept 2018). Recruitment of participants began in October 2018. Implementation of the bundle commenced in November 2018, and data collection will end in May 2021.

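### Rules on declining clinicians and withdrawn cases could let cases leave the DAOH90 comparison unevenly between phases; the primary population should be fixed as every eligible operation by department phase

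*Protocol article*

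**What the plan says.** All places are in the protocol article.

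- **Inclusion criteria** takes in all hip or knee arthroplasty and cardiothoracic surgery; these "procedures will be carried out in the five clusters under general anaesthesia with or without regional anaesthesia", or under regional anaesthesia with sedation. It then adds a clinician condition: "Participant anaesthetists, anaesthetic technicians and perfusionists who consent to be part of the study will be included".
- **Exclusion criteria** removes transplant recipients and organ donors, and then states: "Participant anaesthetists, anaesthetic technicians and perfusionists who decline to be part of the study will be excluded". No phase is named.
- **Withdrawal criteria** begins: "Participating anaesthetists will be expected to act in the best interests of their patients". On that ground they "will be free to withdraw individual cases or to omit any aspect of the bundle", and they are asked to report such decisions.
- **Primary outcome** says DAOH90 comes from a national dataset and can be collected for all patients.
- **Design** has the one exclusion expressly tied to the analysis: the week after transition at each site.
- **Blinding, concealment and cross-contamination** says that neither blinding nor concealment is possible.
- **Dates.** The caption of Fig. 2 says: "Baseline data collection will be from 20 May 2018". Trial status says: "Recruitment of participants began in October 2018". Setting and participants defines participants as the clinical teams.
- **Data collection** lists the patient-level data. No anaesthetist identity or consent status is among them.

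**The concern.** In a department-randomised comparison, the analysed cases should not depend on choices that individual clinicians make with the phase known. Two stated rules open that door. The clinician exclusion stands under the same heading as the patient exclusions. The withdrawal rule offers withdrawing a case as an alternative to omitting a bundle element, so it can be read as meaning more than non-adherence. The all-procedures and all-patients wording points the other way.

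If cases do leave, the two phases are unlikely to lose them equally. Withdrawing a case has practical meaning mainly once the bundle is in use, and part of the control period came before any clinician could consent or decline. The omnibus test is a rank sum test with no covariates; covariates enter only through quantile regression. The rank test therefore could not correct for selective removal of patients with a poor prognosis.

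**Working it through.** **No plan figure to reproduce.** The article gives no expected share of declined or withdrawn cases. Its power figures (100% for the rank sum test, 77.7% for quantile regression) come from simulations on site distributions that are not given, so no closed formula reproduces them. The 5492 cases per group from Statistics and sample size is used below.

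**Control time before clinician recruitment.** From 20 May to 1 October 2018 is 134 days. Step 1 lasts 180 days, with all five sites under control. Control cluster-periods total 5 + 4 + 3 + 2 + 1 = 15, or 15 × 180 = 2700 cluster-days. With equal caseloads (an assumption) the share is 5 × 134 / 2700 = 670 / 2700 = 25%. The article gives only the month; a start on 31 October would make it 5 × 164 / 2700 = 30%.

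**Effect of removal on the rank sum test.** Assumptions: no true effect; 5492 cases per group before removal; a share w removed from the active phase only; removed cases drawn evenly from the lowest fraction q of DAOH90 ranks; ties and clustering ignored. The values of w and q are assumed, not taken from the document.

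- Mean rank of the kept active cases: m = (0.5 − w·q/2) / (1 − w)
- n0 = 5492, n1 = 5492·(1 − w)
- SE = √[(n0 + n1 + 1) / (12·n0·n1)]
- z = (m − 0.5) / SE, then the two-sided rejection rate at 5%

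For w = 2%, q = 0.25:

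- m = (0.5 − 0.0025) / 0.98 = 0.5077
- n1 = 5382, SE = 0.00554
- z = 1.38, rejection rate 28%

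| Share removed | Lowest quarter | Lowest half | At random |
|---|---|---|---|
| 1% | z 0.69, 10.5% | z 0.46, 7.4% | z 0, 5% |
| 2% | z 1.38, 28% | z 0.92, 15% | z 0, 5% |
| 5% | z 3.54, 94% | z 2.36, 65% | z 0, 5% |

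If cases from the top half are removed instead, z is −0.92 at 2% and −2.36 at 5%, that is, against the bundle.

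**Effect on the quantile of interest.** With 2% removed from the lowest quarter, the observed 25th centile in the active phase is the true centile 0.25 × 0.98 + 0.02 = 26.5%. Quantile regression at 0.25 is therefore shifted as well.

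**With all eligible cases kept**, w = 0 in both phases, this bias is zero and 5492 per group is unchanged.

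**The case against.** The strongest reply is that no sentence removes these patients' records from the DAOH90 analysis. The exclusion sentence names clinicians, and where patients are meant the same section says so. Withdrawing a case, placed beside omitting a bundle element, can be read as withdrawal from the bundle. With no anaesthetist identifier listed and baseline data older than clinician recruitment, consent may never filter the outcome dataset at all. The analysis population may also be defined in a statistical analysis plan that is not shown.

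Much of this stands, and it limits the point. A reader might infer that these cases definitely leave the study, that they leave only from the intervention phase, and that the result is biased in favour of the bundle. The document supports none of these as fact:

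- Departure from the analysis is a reading of the rules, not an express statement.
- Neither rule names a phase. Usual care is itself defined by what each participating anaesthetist does, and 10 of the 15 control cluster-periods follow Step 1. Decliners' cases could be dropped from both phases or from neither.
- The direction is plausible for withdrawals made in the patient's interest. For decliners no reason is given, and bias could be nil or reversed.

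The reply does not dispose of the point. Eligibility and withdrawal are stated here, and the wording supports two incompatible populations. This article also settles other analysis-set questions itself: the one-week exclusion, and counting patients still in hospital at rollout as baseline. The criticism is of rules as written, not of an omitted detail.

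**Conclusion.** The point holds conditionally. The stated rules can be read as letting cases leave a department-randomised, unblinded comparison, and the same article points to all procedures and all patients. If cases do leave, the removal would fall mainly on the active phase.

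The size is illustrative. Removing 2% of active-phase cases would raise the false-positive rate from 5% to about 28% or 15%, depending on whether they come from the lowest quarter or the lowest half of DAOH90; random removal would not raise it. These rates rest wholly on assumed shares and ranks and on a plain rank sum test. The Discussion describes the test as tailored to a stepped wedge, and such a version would have a different standard error. The figures show that a small selective loss could matter; they do not show that it will occur.

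**What to change.** State that the primary analysis includes every eligible operation in the five departments, classified by the phase its department was scheduled to be in on the date of surgery, regardless of clinician consent, case withdrawal or bundle adherence. Keep the stated one-week transition exclusion and the transplant and donor exclusions. Report withdrawn cases by phase as non-adherence. The clinicians' freedom to withdraw a case or omit an element is untouched; only its consequence for the analysis is settled.

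This takes about two sentences and no new outcome data, since DAOH90 is described as available for all patients. There are two modest costs. Cases managed without the bundle will dilute the effect slightly. It should also be confirmed that the ethics approval, which rests on anonymous patient data and clinician consent, covers routine data from the cases of clinicians who decline.
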